**Table 4. Guidelines for Study Treatment Modifications**

| Immune-Related AE a | Severity
(NCI CTCAE v5.0) | Treatment Modification |
|--------------------------------|------------------------------|------------------------|
| IRR (Appendix 12.6)            | Grade 1 to 3                 | Appendix 12.6          |

CONFIDENTIAL

May not be used, divulged, published, or otherwise disclosed without the consent of  
Molecular Partners AG, Schlieren, Switzerland

| Immune-Related AE a | Severity
(NCI CTCAE v5.0)                                                                                                                                                             | Treatment Modification                                                                                                                                                                                                                                                                                                                                                                                                                       |
|---------------------------------------|--------------------------------------------------------------------------------------------------------------------------------------------------------------------------------------------------|-----------------------------------------------------------------------------------------------------------------------------------------------------------------------------------------------------------------------------------------------------------------------------------------------------------------------------------------------------------------------------------------------------------------------------------------------------|
|                                       | Grade 4 or recurrent Grade 3 (that cannot be adequately treated with standard-of-care)                                                                                                           | Permanently discontinue                                                                                                                                                                                                                                                                                                                                                                                                                             |
| CRS (Appendix 12.7)                   | Grade 1 to 3                                                                                                                                                                                     | Withhold until clinical improvement of symptoms according to Investigator judgement. Re-start at 50% of infusion rate of the current infusion and increase gradually.                                                                                                                                                                                                                                                                               |
|                                       | Grade 4 or recurrent Grade 3 (that cannot be adequately treated with standard-of-care)                                                                                                           | Permanently discontinue                                                                                                                                                                                                                                                                                                                                                                                                                             |
| Non-infectious pneumonitis            | Grade 2                                                                                                                                                                                          | Withhold until recovered to Grade 0 to 1 a                                                                                                                                                                                                                                                                                                                                                                                               |
|                                       | Grade 3 or 4 or recurrent Grade 2                                                                                                                                                                | Permanently discontinue                                                                                                                                                                                                                                                                                                                                                                                                                             |
| Non-infectious colitis                | Grade 2 or 3                                                                                                                                                                                     | Withhold until recovered to Grade 0 to 1 a                                                                                                                                                                                                                                                                                                                                                                                               |
|                                       | Grade 4 or recurrent Grade 3                                                                                                                                                                     | Permanently discontinue                                                                                                                                                                                                                                                                                                                                                                                                                             |
| Non-infectious nephritis              | Grade 2 with serum creatinine > 1.5 x ULN to ≤ 3 x ULN                                                                                                                                           | Withhold until recovered to Grade 0 to 1 a                                                                                                                                                                                                                                                                                                                                                                                               |
|                                       | ≥ Grade 3 with serum creatinine > 3 x ULN                                                                                                                                                        | Permanently discontinue                                                                                                                                                                                                                                                                                                                                                                                                                             |
| Endocrinopathies                      | Symptomatic hypophysitis
Diabetes mellitus type 1 associated with ≥ Grade 3 hyperglycemia (glucose > 250 mg/dL or > 13.9 mmol/L) or associated with ketoacidosis
Hyperthyroidism ≥ Grade 3 | Withhold until recovered to Grade 0 to 1 a
For patients with Grade 3 or 4 endocrinopathy that improved to Grade 2 or lower and is controlled with hormone replacement, if indicated, continuation of study treatment may be considered after corticosteroid taper, if needed. Otherwise treatment should be permanently discontinued.
Hypothyroidism may be managed with replacement therapy without study treatment interruption. |
| Non-infectious hepatitis              | Grade 2 with AST or ALT ≥ 3 to 5 x ULN or total bilirubin > 1.5 to 3 x ULN                                                                                                                       | Withhold until recovered to Grade 0 to 1 a                                                                                                                                                                                                                                                                                                                                                                                               |
|                                       | ≥ Grade 3 with AST or ALT > 5 x ULN or total bilirubin > 3 x ULN                                                                                                                                 | Permanently discontinue                                                                                                                                                                                                                                                                                                                                                                                                                             |
|                                       | In case of liver metastasis with screening Grade 2 elevation of AST or ALT, hepatitis with AST or ALT increases ≥ 50% and lasts ≥ 7 days                                                         | Permanently discontinue                                                                                                                                                                                                                                                                                                                                                                                                                             |

CONFIDENTIAL

May not be used, divulged, published, or otherwise disclosed without the consent of  
Molecular Partners AG, Schlieren, Switzerland

| Immune-Related AE a         | Severity
(NCI CTCAE v5.0)                                                                                                  | Treatment Modification                                |
|----------------------------------------|-------------------------------------------------------------------------------------------------------------------------------|-------------------------------------------------------|
| Skin reactions                         | Grade 3 or suspected Stevens-Johnson syndrome (SJS) or toxic epidermal necrolysis (TEN)                                       | Withhold until recovered to Grade 0 to 1 a |
|                                        | Grade 4 or confirmed SJS or TEN                                                                                               | Permanently discontinue                               |
| Other immune-related adverse reactions | Based on severity and type of reaction (Grade 2 or 3)                                                                         | Withhold until recovered to Grade 0 to 1 a |
|                                        | Grade 3 or 4 myocarditis
Grade 3 or 4 encephalitis
Grade 3 or 4 Guillain-Barré syndrome
Recurrent Grade 3 or Grade 4 | Permanently discontinue                               |
| Tumor lysis syndrome                   | Grade 3 or 4                                                                                                                  | Permanently discontinue                               |

a If an immune-related AE does not resolve to Grade 0 to 1 within 3 weeks after last study drug administration or if corticosteroid dosing cannot be reduced to  $\leq 10$  mg prednisone or equivalent per day within 3 weeks, study drug administration should be permanently discontinued.

ALT, alanine aminotransferase; AST, aspartate aminotransferase; NCI CTCAE, National Cancer Institute Common Terminology Criteria for Adverse Events; SJS, Stevens-Johnson syndrome; TEN, toxic epidermal necrolysis; ULN, upper limit of normal.

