### 5.2 Study Treatment Schedule and Administration

#### 5.2.1 Study Drug Dose

For each patient, the assigned dose of MP0317 will be based on the available cohort as recommended by the DERC. For the dose-escalation study part on a q3w schedule, the starting dose is 0.03 mg/kg q3w and up to 6 q3w dose levels are planned, as shown in Table 3. The doses to be evaluated on a q1w schedule in the dose-escalation part are shown in Table 3. A treatment cycle will be 3 weeks (21 days), with DLT evaluation period of 4 weeks after first study drug administration. See Section 5.2.9 for study treatment modifications.

[figure not shown]The table content is completely redacted with black boxes.

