### 5.2.5 Dose-Limiting Toxicities

DLT evaluation and a recommendation regarding dose-escalation steps will be made by the DERC (Section 8.5), after consideration of all available safety information.

A DLT is defined as an AE or abnormal laboratory result meeting any of the criteria below, that is assessed by the Investigator as related to study treatment, and that occurs within the DLT evaluation period, including death (Section 5.2.6). Severity of all AEs will be assessed according to NCI CTCAE v5.0.

- Any  $\geq$  Grade 3 study drug-related non-hematologic AE, including the following abnormal laboratory results: Hepatic laboratory parameters potentially fulfilling Hy's Law criteria: AST or ALT  $\geq 3 \times$  ULN and concomitant total bilirubin  $\geq 2 \times$  ULN
- Any Grade 4 study drug-related hematologic AE or abnormal laboratory result (hematologic or non-hematologic)
- Grade 3 neutropenia lasting  $> 7$  days despite adequate standard-of-care medication
- Grade 3 or 4 febrile neutropenia (fever  $\geq 38.5$  °C)
- Grade 3 anemia that cannot be adequately treated by blood transfusions
- Inability to administer the next dose due to a drug-related AE or delayed administration of the next dose due to a drug-related AE and/or abnormal laboratory result lasting  $> 14$  days despite adequate medication
- Any other AE/abnormal laboratory result which, in the view of the Investigator and/or Sponsor, is deemed clinically significant and considered a DLT

Note that the following AEs/abnormal laboratory results, some of which are expected with the study treatment, will not be considered a DLT:

- Any transient Grade 3 or 4 abnormal laboratory results without any related clinical symptoms and lasting  $< 72$  h
- Grade 3 events that have not been optimally treated with standard-of-care medication, lasting  $< 7$  days
- Grade 4 amylase or lipase not associated with symptoms or clinical manifestations or radiologic signs of pancreatitis

- Grade  $\geq 3$  lymphocytopenia not associated with symptoms or clinical manifestations
- Grade 3 hypertension resolving within 48 h
- Grade 3 IRR resolving under adequate treatment (first event only)
- Grade 3 fatigue lasting  $\leq 14$  days

An AE considered by the Investigator to be disease-related should not be considered a DLT.

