### 5.2.9 Treatment Modification (Delay, Interruption)

Guidelines for study treatment modifications are shown in Table 4.

The following should be taken into consideration:

- If supportive care is ineffective, drug administration delays or infusion interruptions should be considered to prevent worsening of the related AE(s).
- Drug administration delays or infusion interruptions may be implemented for Grade 1 related AEs if the Investigator feels it is in the interests of the patient's safety.
- Drug administration delay for any reason is allowed for up to 3 weeks. Re-starting treatment after a delay longer than 3 weeks may be allowed with approval of the Sponsor. During such delay, a limited set of study assessments/visits may be performed as determined by the Investigator in consultation with the Sponsor.
- Guidelines for the management of IRRs and CRS are provided in Appendix 12.6 and Appendix 12.7, respectively.
- Any treatment modifications such as drug administration delays or infusion interruptions should be entered in the eCRF.

Study treatment should be permanently discontinued for Grade 4 or recurrent Grade 3 AEs, unless otherwise specified in Table 4.

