**Table 5. Time Windows for Administration of Study Treatment (Q3W)**

| Treatment Cycles                   | Allowed Time Window |
|------------------------------------|---------------------|
| For Dose-Escalation Cohorts |                     |
| Between Cycle 1 and 2              | 21 + maximum 2 days |
| From Cycle 2 to Cycle 4            | 21 $\pm$ 2 days     |
| From Cycle 5 onwards               | 21 $\pm$ 3 days     |
| For Safety Expansion Cohort |                     |
| From Cycle 1 to Cycle 4            | 21 $\pm$ 2 days     |
| From Cycle 5 onwards               | 21 $\pm$ 3 days     |

CONFIDENTIAL

May not be used, divulged, published, or otherwise disclosed without the consent of  
Molecular Partners AG, Schlieren, Switzerland

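### On q3w the recovery limit in Table 4 footnote a runs out on the day the next dose is due, while Section 5.2.9 allows a further 3 weeks, and no text says which rule prevails

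*Protocol*

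**What the plan says.** Three places in the protocol bear on the same patient.

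- **Table 4 and its footnote a.** For non-infectious pneumonitis, colitis, nephritis and hepatitis, endocrinopathies, skin reactions and other immune-related reactions, at the grades listed, the action is to withhold drug until recovery to Grade 0 or 1. Footnote a is attached to that action. It sets the consequence of slow recovery: "If an immune-related AE does not resolve to Grade 0 to 1 within 3 weeks after last study drug administration", then "study drug administration should be permanently discontinued". A second limb applies the same consequence "if corticosteroid dosing cannot be reduced to" the stated daily prednisone level within 3 weeks. That limb does not say from when the 3 weeks run.
- **Section 5.2.9, bullets above the table.** "Drug administration delay for any reason is allowed for up to 3 weeks", and a restart after a longer delay is possible if the Sponsor approves. The only cross-reference to Table 4 as an exception sits in a separate sentence, on Grade 4 and recurrent Grade 3 events.
- **Section 5.2.5, DLT criteria.** One criterion is "Inability to administer the next dose due to a drug-related AE". The same bullet also counts a drug-related delay of the next dose lasting more than 14 days.

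The dosing interval comes from Section 5.2.1: "A treatment cycle will be 3 weeks (21 days". In Table 5 the first interval in q3w escalation cohorts is "21 + maximum 2 days", so it can be lengthened but not shortened.

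**The concern.** A limit on how long drug may be withheld needs a starting point that leaves some time to withhold it. Footnote a starts its clock at the last dose. On q3w the clock and the dosing interval have the same length, so an event that has resolved when the limit expires has delayed nothing, and an event that has not resolved ends treatment. Section 5.2.9 measures a delay, which naturally starts when the dose was due. It gives the same patient up to 3 more weeks.

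Two things are at stake. The first is who stays on treatment, because two sites following different passages would handle the same event differently. The second is the DLT count. Cycle 2 Day 1 falls inside the 4-week DLT evaluation period, and being unable to give the next dose is a DLT criterion. Which passage a site follows may therefore decide whether a related Grade 2 event enters the dose-escalation model as a DLT.

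**Working it through.** **1. Timeline.** Inputs: footnote limit of 21 days from the last dose (Table 4); delay allowance of 21 days, taken to run from the scheduled dosing day (Section 5.2.9); interval of 21 days on q3w (Section 5.2.1) and 7 days on q1w (dosing on Days 1, 8 and 15, Table 14); q3w windows from Table 5.

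- Longest event-driven delay under footnote a = max(0, 21 − interval)
- Latest restart without Sponsor approval under Section 5.2.9 = interval + 21

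| Case | Dose due (day after last dose) | Delay left by footnote a | Latest restart, footnote a | Latest restart, 5.2.9 |
|---|---|---|---|---|
| q3w, on schedule | 21 | 21 − 21 = 0 days | day 21 | 21 + 21 = day 42 |
| q3w, later dose planned 2 days early | 19 | 21 − 19 = 2 days | day 21 | 19 + 21 = day 40 |
| q3w, Cycle 5 onwards, planned 3 days early | 18 | 21 − 18 = 3 days | day 21 | 18 + 21 = day 39 |
| q1w | 7 | 21 − 7 = 14 days | day 21 | 7 + 21 = day 28 |

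On q3w, an event that resolves between day 22 and day 42 leads to permanent discontinuation under one passage and to a permitted restart under the other. Beyond day 42 one passage still requires discontinuation and the other refers the decision to the Sponsor. The early-window rows do not exist between Cycles 1 and 2 in escalation cohorts, where DLTs are counted, because that window only extends the interval. Section 5.2.10 also limits these windows to reasons other than adverse events.

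**2. DLT classification.** Take a q3w escalation patient with a related Grade 2 event in Cycle 1 that is still open on day 21.

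- Under footnote a, treatment stops. Dose 2 is not given because of a drug-related event, which can be read as the inability criterion, hence a DLT.
- Under Section 5.2.9, the dose is delayed. A delay of 14 days or less does not meet the delay criterion. A delay of 15 to 21 days does meet it, although Section 5.2.9 permits it.

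The two readings therefore differ on DLT status for delays of up to 14 days, that is, recovery by day 21 + 14 = 35.

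**3. What one DLT does in the model.** Table 30 Setting 1 has 0/3 at every dose. Setting 2 has 1/3 at the current dose and 0/3 below it. Section 9.4.1.1 excludes a dose whose probability of excessive toxicity is more than 25%. As a check, I recomputed the posterior by numerical integration from the Table 23 prior and the Section 9.4.1.2 model.

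| Current dose (mg/kg) | Next dose (mg/kg) | P(overdose) at next dose, 0/3 | P(overdose) at next dose, 1/3 | Recomputed, 1/3 | Crosses 25%? |
|---|---|---|---|---|---|
| 0.10 | 0.30 | 0.016 | 0.193 | 0.190 | no |
| 0.30 | 1.00 | 0.032 | 0.241 | 0.235 | no |
| 1.00 | 3.00 | 0.055 | 0.306 | 0.303 | yes |
| 3.00 | 10.00 | 0.084 | 0.384 | 0.389 | yes |

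For 0/3 at 1.00 mg/kg the recomputed value at 3.00 mg/kg is 0.053, against 0.055 in Table 30. For 0/3 at 0.30 mg/kg, Table 30 prints both 0.032 and 0.063 for the next dose. The recomputed value is 0.031, and either printed figure is far below 25%.

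**The case against.** The best defence is that a specific rule sits inside a general one. Section 5.2.9 gives a permissive ceiling among points to be considered, and footnote a is a stricter rule for immune-related events. A site that follows the footnote breaks neither text. That is a common structure, but the protocol does not state it. If the footnote does prevail, the withhold action repeated through Table 4 has almost nothing to act on under q3w, the schedule the trial starts with.

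Several stronger readings are tempting and are not supported.

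- A reader might infer that withholding can never be applied. On q1w the footnote leaves 14 days. On q3w an early-planned later dose leaves 2 to 3 days, and the corticosteroid limb has no stated start, so a short delay for tapering is conceivable.
- A reader might see a second contradiction in the endocrinopathy row. That row opens its own route, "For patients with Grade 3 or 4 endocrinopathy that improved to Grade 2 or lower and is controlled with hormone replacement", with discontinuation otherwise. It reads naturally as an exception to the footnote and needs only confirmation.
- A reader might infer that Section 5.2.9 always means no DLT. It does not, because a drug-related delay of more than 14 days is itself a criterion.
- A reader might infer that one reclassified patient always blocks escalation. At 0.10 and 0.30 mg/kg it does not, and the dosing decision rests with the DERC and the Sponsor on all the data.
- A reader might fear a biased comparison of q3w with q1w. None is planned, and the protocol treats the schedules' decision rules and MTDs as independent.

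Two further cautions stand. It is an inference that a protocol-directed stop for a Grade 2 event counts as inability to dose, since the 14-day qualifier could be read as covering both limbs of that bullet. Related non-hematologic events of Grade 3 or above are generally DLTs already, so the added effect is mainly on Grade 2 events.

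**Conclusion.** The inconsistency is real and should be fixed. On q3w, footnote a and Section 5.2.9 differ by 21 days on the last permitted restart (day 21 against day 42). On q1w they differ by 7 days (day 21 against day 28). The protocol does not rank them. For q3w immune-related events the withhold action leaves essentially no delay, and none at Cycle 2 Day 1 in escalation cohorts.

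The effect on DLT counting is possible but conditional. It needs a related Grade 2 event open at Cycle 2 Day 1, a site that reads the footnote stop as inability to dose, and recovery that would have allowed dosing within 14 days of the due date. Counting the alternative as 0/3 also assumes that the delayed patient remains evaluable under Section 5.2.6. In that case one DLT at 1.00 or 3.00 mg/kg carries the next dose across the 25% limit, and one at 0.10 or 0.30 mg/kg does not. The protocol gives no basis for saying how often this would happen. The timeline assumes that the Section 5.2.9 delay is counted from the scheduled dosing day.

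**What to change.** Reconcile Section 5.2.9 and Table 4 footnote a in the next amendment:

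1. Name one starting point for the 3-week clock in both places, and give the corticosteroid limb a starting point too.
2. State which rule takes precedence for immune-related events, and whether the Sponsor-approval route remains open for them.
3. Write out the resulting last restart day for q3w and for q1w.
4. State in Section 5.2.5 how a discontinuation under footnote a is classified under the inability-to-dose criterion.
5. Confirm that the endocrinopathy row is an exception to the footnote.

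The clinical limit itself is for the sponsor to decide. The cost is a wording change to one footnote, one bullet and one DLT criterion, with no added patients, visits or procedures.
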